### **5.3 Dropout and Disqualification Criteria**

Subject may stop participation at any time upon request or be dropped by the decision of the investigator or client for safety, behavioral, or administrative reasons at any time. The investigator shall question the subject regarding the grounds for dropout and return all investigational products not taken by the subject as well as requesting for a last visit and making maximum effort to perform follow-up observations for adverse events not resolved at the time

when applicable.

Instances when the subject may stop clinical trial are as below.

- ① When the subject or legal representative of subject withdraws consent for clinical trial participation
- ② Violation of inclusion/exclusion criteria
- ③ Violation of test plan outlined in the clinical trial plan
- ④ When there is an issue in administration of investigational product for subject
- ⑤ When subject cannot be traced
- ⑥ Instances where participation in clinical trial is deemed inappropriate by the investigator

#### **5.4 Clinical Trial Compliance and Action for Plan Violation**

Supervisor and instructor for this clinical trial shall understand and strictly perform the clinical trial according to the plan to prevent violations of clinical trial plan. The clinical trial supervisor shall conduct telephone monitoring and send out written notifications regarding future visiting hours as well as taking appropriate action for subjects for visitation for compliance with clinical trial administration and examination schedule. Violations of clinical trial plan which occur despite such efforts will be processed as below.

Critical violations of clinical trial plan will result in disqualification of corresponding subject from analysis(Excluding PPS) by principle and the conditions are as listed below.

- ① Lack of consent form
- ② Violation of inclusion/exclusion criteria
- ③ Administered with prohibited co-administered drugs during clinical trial period
- ④ Omission of major examination in the trial period

Other minor violations of clinical trial plan that are deemed to not affect other matters and interpretation of study results will be included in the PPS analysis after overall observation whether such violations have impacted the study

conducted by the investigator, client, monitor, and statistician when writing the conclusion report by listing the exact details and reason of violation or delay.

## 6. INVESTIGATIONAL PRODUCTS

### 6.1 Overview of Investigational products

#### 6.1.1 Study drug

- Name: Pelubi CR tablet(Pelubiprofen 45mg)
- Property/Form: Round, light yellow slow release tablet with film coating
- Storage method: Sealed container without light exposure in room temperature(1~30℃)
- Expiration: 36 months
- Ingredients and content: 1 Tablet

| Purpose         | Substance    | Spec. | Amount | Unit |
|-----------------|--------------|-------|--------|------|
| Main ingredient | Pelubiprofen |       | 45.0   | mg   |

#### 6.1.2 Control Drug

- Name: Airtal tablet(Aceclofenac 100mg)
- Property/Form: Coated white tablet
- Storage method: Sealed container without light exposure in room temperature
- Expiration: 36 months
- Ingredients and content: 1 Tablet

| Purpose         | Substance   | Spec. | Amount | Unit |
|-----------------|-------------|-------|--------|------|
| Main ingredient | Aceclofenac | EP    | 100.0  | mg   |

#### 6.1.3 Study drug Placebo

- Name: Pelubi CR tablet(Pelubiprofen) placebo
- Property/Form: Round, light yellow slow release tablet with film coating
- Storage method: Sealed container without light exposure in room temperature(1~30℃)
- Expiration: 36 months

#### 6.1.4 Control Drug Placebo

- Name: Airtal tablet(Aceclofenac) placebo
- Property/Form: Coated white tablet

- Storage method: Sealed container without light exposure in room temperature
- Expiration: 36 months

#### 6.1.5 Rescue drug

- Name: Tylenol ER tablet 650mg
- Property/Form: White rectangular film coated tablet
- Storage method: Sealed container without light exposure in room temperature
- Expiration: 36 months
- Ingredients and content:

| Purpose         | Substance     | Spec. | Amount | Unit |
|-----------------|---------------|-------|--------|------|
| Main ingredient | Acetaminophen |       | 650.0  | mg   |

#### 6.2 Dosage, Administration Method, Administration Period

- Study drug : Oral administration of 1 Pelubi CR tablet(Pelubiprofen 45mg) after meal twice per day and take without breaking or chewing since it is a slow release tablet.
- Control drug : Oral administration of 1 Airtal tablet(Aceclofenac 100mg) after meal twice per day

| Group         | Morning                                      | Evening                                      |
|---------------|----------------------------------------------|----------------------------------------------|
| Test Group    | 1 Pelubi CR tablet + 1 Airtal tablet placebo | 1 Pelubi CR tablet + 1 Airtal tablet placebo |
| Control Group | 1 Pelubi CR tablet placebo + 1 Airtal tablet | 1 Pelubi CR tablet placebo + 1 Airtal tablet |

#### 6.3 Production, Packaging, and Labeling of Investigational products

Investigational products are supplied to the managing pharmacist of clinical trial performing institution after the client manufactures or purchases the drugs.

Items listed on investigational products shall comply with Article 69 Clause 6 of the Regulation on Safety of Drugs, etc. and lists the following.

Sample production and maintenance methods for double-blind are as below.

- ① Separate storage : Study drugs and control drugs are stored separately by manufacturing number until labeling to prevent confusion.
- ② Labeling : Manufacture the label including the following details.

- |                                                                                                                                                                                                                                                                                                                                                                                                                                                                                        |
|----------------------------------------------------------------------------------------------------------------------------------------------------------------------------------------------------------------------------------------------------------------------------------------------------------------------------------------------------------------------------------------------------------------------------------------------------------------------------------------|
| 

1. Indication of "For clinical trial"

2. Code name of product or generic name of main ingredient

3. Manufacturing number and expiration date or reinspection date

4. Storage method

5. Name and address of party approved for clinical trial plan

6. Indication of "Cannot use for purposes other than clinical trial"

7. Serial number: Recorded according to random assignment chart

 |
|----------------------------------------------------------------------------------------------------------------------------------------------------------------------------------------------------------------------------------------------------------------------------------------------------------------------------------------------------------------------------------------------------------------------------------------------------------------------------------------|

- ③ Subdivided packaging : Drugs shall be subdivided and packaged by test group and control group according to 「3.4 Assignment of Administration Group」. Drugs shall be packaged sequentially to prevent confusion between test group and control group in terms of dosage and administration during subdivided packaging and stored separately until labeling. Investigational products(Study drug or control drug) shall be packaged by assignment code as below.

| Group         | Morning                                      | Evening                                      |
|---------------|----------------------------------------------|----------------------------------------------|
| Test Group    | 1 Pelubi CR tablet + 1 Airtal tablet placebo | 1 Pelubi CR tablet + 1 Airtal tablet placebo |
| Control Group | 1 Pelubi CR tablet placebo + 1 Airtal tablet | 1 Pelubi CR tablet placebo + 1 Airtal tablet |

- ④ Record of packaging and serial number: Drugs shall be packaged in quantity for 17 days(14 days+Extra 3 days; 34 packages) according to scheduled visits for each group and labeling listed in item ② above shall be performed for packaged drugs and each packaging shall be labeled as "Investigational product".
- ⑤ Rescue drug shall be packaged individually.

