| Hematology test      | WBC, RBC, Hemoglobin, Hematocrit, Platelet count, WBC Diffcount                                                                                                                     |
| Blood chemistry test | Na, K, Ca, Cl, BUN, Creatinine, Uric acid, Total bilirubin, Albumin, Total protein, Creatine Kinase, ALT, AST, r-GT, Alkaline phosphatase, glucose, Total cholesterol, Triglyceride |
| Urine test           | Protein, Glucose, Urobilinogen, WBC, RBC                                                                                                                                            |
  - 5 Coagulation test      PT, aPTT  
                                 Performed during Visit 1.
  - 6 Image knee AP. Lateral and it can be omitted if there are test results within past 4 weeks.
  - 7 Perform hCG test through urine for women of childbearing age.
  - 8 Medication of pain reliever 24 hours prior to the visit is restricted and visits can be rescheduled upon medication within visit window.

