#### **4.2.3 Visit 3(Intermediary Visit, Day 14±3)**

This visit takes place on day 14 after initial administration of investigational products and evaluates the following items.

- 1) Check for changes in co-administered drugs compared to previous visit.
- 2) Investigate for occurrence of adverse events and its details.
- 3) Measure vital signs and weight and conduct physical examination.
- 4) Evaluate 100mm Pain VAS.
- 5) Evaluate K-WOMAC.

- 6) Evaluate Patient Global Assessment.
- 7) Train on administration method and distribute investigational products.
- 8) Recover residual clinical trials from the subject and record residual quantity.
- 9) Distribute new rescue drug.
- 10) Train on rescue drug log writing and distribute new rescue drug log.
- 11) Schedule next visit.

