#### **4.2.4 Visit 4(End of Clinical Trial, Day 28±3)**

This visit takes place on the last day of the study for final effectiveness evaluation of subjects administered investigational products for 28 days. Also, the following items are evaluated even if the clinical trial ends prematurely.

- 1) Check for changes in co-administered drugs compared to previous visit.
- 2) Investigate for occurrence of adverse events and its details.
- 3) Measure vital signs and weight and conduct physical examination.
- 4) Conduct laboratory tests(Hematologic test, blood chemistry test, urine test).
- 5) Conduct pregnancy test for female subjects of childbearing age.
- 6) Perform ECG.
- 7) Evaluate 100mm Pain VAS.
- 8) Evaluate K-WOMAC.
- 9) Evaluate Patient Global Assessment.
- 10) Recover residual clinical trials from the subject and record residual quantity.

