## **6.6 Compliance Assessment**

Investigational product compliance shall be examined by the investigator in comparison of residual amount of investigational product brought by the subject upon every visit. Residual amount after administration must be returned to the pharmacy and recorded on dispense records. Remaining quantity after administration of rescue drug must also be returned to the pharmacy and recorded on dispense records.

$$\text{Drug compliance (\%)} = \frac{\text{Number of actual administrations}}{\text{Number of scheduled administrations}} \times 100$$

\*Number of scheduled administrations: It is calculated by the number of administrations scheduled between the night of visit 2 or 3 and the morning of next visit.

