## **6.7 Co-administered Drugs and Treatment**

### **6.7.1 Permitted Drugs**

Following drugs can be co-administered during clinical trial period.

- 1) Rescue drug (Acetaminophen below dosage of 1,950 mg per day) but administration 24 hours prior to visit is prohibited
- 2) Low dosage aspirin (Maximum daily dosage of 200mg) administered for prevention of cardiovascular disease must be administered without change in dosage until completion of clinical trial. However, administration 24 hours prior to visit is prohibited.
- 3) Co-administered drugs which were administered to the subject prior to participation in this clinical trial deemed to not impact the interpretation of

study results are permitted by decision of clinical trial physician.

- 4) Stomach system related drugs such as proton pump inhibitor and H2-blocker can be administered with prescription when adverse events related to stomach system occur or by decision of clinical trial physician.
- 5) Other drugs used daily for purpose of treatment for other disease and adverse events must be co-administered through consultation with attending physician.

Information(Name, purpose, dosage, administration period, etc.) on all drugs administered(Includes drugs for treatment of other disease and adverse events) shall be recorded in detail in case report for subject.

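### The 17-day pack does not cover every Visit 3 to Visit 4 interval that the windows allow: in 6 of 49 permitted day pairs, supply ends 1 to 3 days before the primary VAS (minor)

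*Protocol*

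**What the plan says.** **Pack size.** Section 6.3, item 4: "Drugs shall be packaged in quantity for 17 days(14 days+Extra 3 days; 34 packages) according to scheduled visits". Section 6.2 gives twice-daily dosing in both arms. The Clinical Trial Schedule prescribes investigational product at Visits 2 and 3 only.

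**Visit windows.** Section 4.2.3 puts Visit 3 on Day 14±3 and section 4.2.4 puts Visit 4 on Day 28±3. Each is set on its own; neither refers to the actual date of the other.

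**Doses due and leftovers.** On the number of scheduled administrations, section 6.6 says: "It is calculated by the number of administrations scheduled between the night of visit 2 or 3 and the morning of next visit". The same section has the residual amount returned to the pharmacy.

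**Moving a visit.** Footnote 8 of the schedule: "Medication of pain reliever 24 hours prior to the visit is restricted and visits can be rescheduled upon medication within visit window". Section 6.7.1 permits rescue acetaminophen with the same restriction: "Rescue drug (Acetaminophen below dosage of 1,950 mg per day) but administration 24 hours prior to visit is prohibited".

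**Length of treatment.** Section 4.2.4 describes Visit 4 as the "final effectiveness evaluation of subjects administered investigational products for 28 days", and section 3.1 also gives 28 days. Section 6.2 is headed "Dosage, Administration Method, Administration Period" but states no period.

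**Endpoint and analysis set.** The primary variable is the change in VAS at Day 28 (7.1.1), measured at Visit 4. The PPS is the main analysis set (7.2.2).

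**The concern.** The three extra days in the pack mirror the ±3 days of one visit window. That covers a late Visit 4 after an on-time Visit 3. It does not fully cover a late Visit 4 after an early Visit 3, because the second pack starts early and must also last late.

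Footnote 8 is a foreseeable way to reach a late Visit 4. A patient who took rescue drug in the last 24 hours can be rebooked within the window, and nothing requires a check of the remaining supply.

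At stake is the state in which some patients give the primary reading. A patient who broke no rule could be assessed 1 to 3 days after the last supplied dose. Readings off drug in both arms would tend to shrink a true difference between them, which is the unsafe direction in a noninferiority comparison.

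**Working it through.** **1. Reproduce the plan's figure.** 17 days × 2 doses = 34 packages, as stated in 6.3.

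**2. First pack.** Visit 2 is Day 1 and Visit 3 is at the latest Day 17. Doses due = 2 × (17 − 1) = 32, which is within 34. The first pack is sufficient.

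**3. Second pack.** On the 6.6 basis, doses due = 2 × (Visit 4 day − Visit 3 day). Visit 3 can be on Days 11 to 17 and Visit 4 on Days 25 to 31, giving 7 × 7 = 49 pairs. The interval runs from 25 − 17 = 8 days to 31 − 11 = 20 days. The pairs above 17 days are:

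| Visit 3, Visit 4 (day) | Interval | Doses due | Supplied | Short by | Highest reachable compliance (6.6 formula) |
|---|---|---|---|---|---|
| 11, 29; 12, 30; 13, 31 | 18 days | 36 | 34 | 2 doses, 1 day | 34/36 = 94.4% |
| 11, 30; 12, 31 | 19 days | 38 | 34 | 4 doses, 2 days | 34/38 = 89.5% |
| 11, 31 | 20 days | 40 | 34 | 6 doses, 3 days | 34/40 = 85.0% |

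That is 6 of 49 pairs. It is a count of permitted combinations, not a probability.

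**4. Where supply ends.** 34 doses starting on the evening of Visit 3 end on the morning of Day (Visit 3 + 17). For Visit 3 on Day 11, 12, 13 or 14 this is Day 28, 29, 30 or 31. Of the three late days (29 to 31), 3, 2, 1 or 0 are uncovered. Supply never ends before the morning of Day 28.

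**5. Share of patients.** The protocol gives no distribution of visit dates, so these are assumptions: normal-density weights on whole days, renormalised within each window.

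| SD of visit timing | A: Visit 4 aimed at Visit 3 + 14 days | B: visits independent |
|---|---|---|
| 1 day | 0.004% (about 0 of 170) | 0.56% (about 1 of 170) |
| 1.5 days | 0.34% (about 0.6) | 3.8% (about 6) |
| 2 days | 1.6% (about 2.8) | 6.7% (about 11) |

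If every permitted pair were equally likely, the share would be 6/49 = 12.2%. The low end is more plausible because sites aim at Day 14 and Day 28. Footnote 8 can push Visit 4 later by an amount that the protocol does not let us size.

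**6. Generous bound on the effect.** Suppose that the true difference equals the full 15 mm margin and vanishes entirely in affected patients. The dilution is 15 × 0.34% = 0.05 mm under A with SD 1.5, and 15 × 3.8% = 0.57 mm under B with SD 1.5. The planned standard error is 24.86 × √(2/85) = 3.8 mm.

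**The case against.** **Treatment is 28 days.** This is the strongest objection. Every statement of treatment length says 28 days, and supply reaches the morning of Day 28 even after a Day 11 Visit 3. A patient runs out only if dosing must continue past Day 28, and the text that implies this is the note to the compliance formula in 6.6, not a dosing instruction. That stands as a limit on the point. It does not remove the conflict: 6.6 then schedules doses for late patients beyond the treatment period, and 6.2 does not settle which reading applies.

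**First-pack leftovers might cover the gap.** A patient seen on Day 11 has used 2 × 10 = 20 of 34 packages and holds 14, more than the worst shortfall of 6. Two packs give 68 doses against at most 2 × 30 = 60 through Day 31. The Visit 3 step on recovering residual material is weak evidence that study drug is collected, because the same line appears at Visit 2, before any study drug has been dispensed. The return of residual drug to the pharmacy in 6.6 is the firmer support. It does not expressly forbid re-dispensing, but no section provides for it.

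**General provisions exist.** Telephone monitoring and visit notices (5.4), sponsor checks of drug quantity (6.4) and unscheduled visits (4.2.5) all help. None caps the interval or provides a top-up.

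**Stronger readings to avoid.** A reader might infer that several patients will run out, that all of them will stay in the PPS, or that the noninferiority result is at risk. The protocol supports none of these. It gives no visit-date distribution, and the likelier assumptions put the number near zero. Section 7.2.1 requires completion according to the plan and 5.4 provides case-by-case review of minor deviations, so PPS membership is likely but not fixed. The bound above is small against the standard error.

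**Conclusion.** The point holds as a small inconsistency between stated numbers: a 17-day pack, two separate ±3-day windows, and doses scheduled to the morning of the next visit. On the 6.6 basis, and with first-pack leftovers returned, 6 of 49 permitted day pairs leave a patient 1 to 3 days (2 to 6 doses) short before the primary VAS. The count and the shortfalls are exact. The number of patients rests on assumed visit timing and is probably between none and a few. No threat to the noninferiority conclusion is shown. The point is minor and worth raising because the remedy is cheap.

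**What to change.** Add to 4.2.4 that Visit 4, including one rescheduled under footnote 8, must fall within Day 28±3 and no more than 17 days after Visit 3. That means by Day 28, 29 or 30 when Visit 3 was on Day 11, 12 or 13. Alternatively, put 40 packages in the second kit, which keeps the full window. Either option takes the 6.6 basis that dosing continues to the morning of Visit 4, and 6.2 should say so.

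**Cost.** The cap is one sentence plus tighter booking after an early Visit 3. A patient seen on Day 11 has no day after Day 28 left for a footnote 8 rescheduling, so Visit 4 should be booked before the cap. The larger kit needs six more double-dummy packages per patient.

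**If dosing is meant to stop at 28 days,** the pack size is adequate and neither change is needed. Late patients are then off drug at Visit 4 whatever the pack holds. Section 6.2 should state the end of dosing, and the dose count in 6.6 should be aligned with it.

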#### **6.4 Management of Investigational products**

- Investigational products shall be stored at room temperature(1~30℃) and they cannot be used without instruction(Prescription) from trial supervisor and instructor.
- The client shall negotiate with the trial supervisor regarding investigational products and dispense the drugs to the managing pharmacist directly and keep a receipt. The investigational products at this time must be indicated "For clinical trial".
- The managing pharmacist shall store and manage investigational products to prevent its usage aside from the purpose of clinical trial.
- The client shall check the quantity and storage of investigational products during clinical trial and take actions for the clinical trial to proceed appropriately.
- The client shall recover and dispose of unused investigational products upon suspension or conclusion of clinical trial or violation of clinical trial plan. The managing pharmacist at this time shall negotiate with the supervisor to return unused investigational products to the client and keep a return receipt.

#### **6.5 Maintenance and Cancellation of Double-blind**

This investigational product shall use double placebos for study drug and control drug for them to be impossible to distinguish by the exterior to maintain double-blind and history of serial number assignment for each group shall be managed by the trial supervisor in sealed state and not disclosed until the conclusion of clinical trial. Even when access to corresponding code is necessary due to occurrence of serious adverse event, the codes shall be managed in the form of double-blind envelope for each subject. However, the trial supervisor may consign such obligations to a person that is deemed appropriate among managing pharmacists or members of research team.

Cancellation of double-blind shall be considered case by case and it should only be considered for severe medical emergencies. Generally, blind must only be canceled when the information regarding the administration group impacts the treatment of subject. When cancellation of blind is deemed necessary by the trial supervisor or the client, the client or the trial supervisor shall make

contact to the other party for consent for cancellation of blind prior to cancellation of blind. Cancellation of blind in such instances shall be recorded and documented.

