## **9. ETHICS AND ADMINISTRATIVE PROCEDURE**

### **9.1 Clinical Trial Plan Compliance**

The investigator must conduct the clinical trial in compliance with the clinical trial plan. The clinical trial cannot be altered from the clinical trial plan unless elimination of immediate risk factors for the subject is necessary and any violations must be recorded with its details and grounds. Even if the investigator determines that the violation of the test plan can improve the performance of clinical trial, the investigator shall not execute the change until agreement from the client and the approval from the IRB(Includes the Director of KFDA if necessary) for the change are given.

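### Section 6.5 considers unblinding only in severe emergencies, yet makes every code break wait for the other party's consent, so prompt access to a subject's envelope is not assured

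*Protocol*

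**What the plan says.** Section 6.5 of the protocol sets out the whole procedure for breaking the blind.

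- **Form of the codes.** With access after a serious adverse event in view, "the codes shall be managed in the form of double-blind envelope for each subject".
- **Custody.** The trial supervisor keeps the codes sealed, but "the trial supervisor may consign such obligations to a person that is deemed appropriate among managing pharmacists or members of research team".
- **When unblinding is considered.** "Cancellation of double-blind shall be considered case by case and it should only be considered for severe medical emergencies". The section adds that, as a general rule, the "blind must only be canceled when the information regarding the administration group impacts the treatment of subject".
- **How it is done.** The next step begins "When cancellation of blind is deemed necessary by the trial supervisor or the client". Whichever of the two has reached that view must then make "contact to the other party for consent for cancellation of blind prior to cancellation of blind". The code break is to be documented.

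Section 9.1, on compliance with the plan, holds a general exception: "The clinical trial cannot be altered from the clinical trial plan unless elimination of immediate risk factors for the subject is necessary". Departures must be recorded with their details and grounds. Section 9.1 does not mention the blind, and section 6.5 does not mention 9.1.

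**The concern.** The consent step falls on exactly the cases where time may matter. Section 6.5 has already ruled out routine requests, so a request that reaches the consent step is by its own terms a severe emergency, and generally one in which the arm affects care. The text asks for consent, not notification, and asks for it before the code is opened. It does not say what happens if the other party cannot be reached or declines.

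The stake is the safety of individual subjects. The protocol's own precautions for the two active drugs (11.1.1 and 11.1.2) list events that can be fatal, including gastrointestinal bleeding and perforation, anaphylactoid reactions and severe skin reactions. They also differ between the drugs: the aceclofenac section lists hypersensitivity to diclofenac and interactions through CYP2C9, which the pelubiprofen section does not. The arm could therefore matter to a treating physician, and 6.5 itself assumes that it can.

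**Working it through.** No formula applies: no sample size, power, error rate or margin enters this point. The check sets section 6.5 against every other section that touches the code, emergencies or serious adverse events.

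**Step 1: does the consent rule apply to emergencies?** Yes. Section 6.5 says of unblinding that "it should only be considered for severe medical emergencies". There is no second class of requests to which the consent rule could be confined.

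**Step 2: is it consent or notification, and when?** Consent, and before the code is opened. The wording of the rule is explicit on both.

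**Step 3: does another section give a separate route to the code?**

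- Section 3.4 says only that the assignment is disclosed after the trial has ended.
- Section 8.4 requires serious adverse events to be reported to the client by phone or fax within 24 hours of the investigator becoming aware of them. This is a reporting duty and gives no access to the code.
- Section 8.5 lists each party's duties after a suspected unexpected serious adverse reaction. None concerns the code.
- Section 9.1 permits departure from the plan to remove immediate risk to a subject. It could cover opening an envelope, but only as a recorded departure from 6.5.

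**Step 4: what does the protocol give in each case?**

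- *The other party is reached and agrees.* The code is opened after the contact. The time taken is not bounded by the document, but it may be short.
- *The other party cannot be reached.* Section 6.5 is silent. The investigator either waits or departs from 6.5 under 9.1.
- *The other party refuses.* Section 6.5 is silent here too, and the same choice remains.

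In the last two cases, prompt access depends on the investigator knowing 9.1, judging that it reaches the blind, and accepting that the act is a departure from the written procedure. That is a fragile basis for an emergency step which the protocol clearly foresees.

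**The case against.** The strongest counter-argument is section 9.1. A severe emergency in which knowing the arm affects treatment is a natural case for an exception based on immediate risk, and a general safety clause need not name every procedure it covers. This stands in part. A reader might infer from 6.5 alone that the protocol has no fallback at all, and that would go too far. What remains is that the fallback is general, unlinked to 6.5, and turns the foreseeable emergency action into a deviation.

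Three other stronger readings are tempting and are not supported.

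- *That the envelopes cannot be used promptly.* The rule sets no waiting period and no form of contact, custody may be delegated to a pharmacist or team member, and 8.4 already uses phone and fax contact with the client. Consent may come quickly. The text supports only that prompt use is not assured.
- *That the site cannot act until the sponsor agrees.* Consent governs opening the code, not treating the patient. Section 5.3 lets a subject be withdrawn for safety at any time, and 6.7.1 allows for drugs given for adverse events. Both arms receive a named, marketed anti-inflammatory drug (6.2) whose precautions are reproduced in the protocol, so the physician knows both candidates without the code.
- *That the rule lets the sponsor influence the results.* The requirement is reciprocal: it also restrains the client from breaking codes on its own. Agreeing to a code break does not reveal the arm, and the client learns of serious adverse events in any case. No bias in the primary analysis can be shown from the document.

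The protocol text reads as a translation, and a softer original is possible. Sites working from this wording would still find prior consent stated plainly.

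**Conclusion.** The point holds as a defect of procedure that should be corrected. Section 6.5 affirmatively makes every code break conditional on the other party's prior consent, in the only situation where it considers a code break, and provides no exception. This is a stated rule and not a detail left to another document. The document does not establish that access would in fact be delayed, that care would be withheld, or that the trial's conclusions are at risk.

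Its size cannot be given as a number. The protocol states neither how often unblinding is expected nor how quickly the other party can be reached. With 190 planned subjects, both arms on drugs of the same class and 28 days of treatment, few cases are likely. For each such subject, the exposure is however long consent takes.

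The conclusion rests on two readings: that the trial supervisor is the responsible investigator on the site's side, and that consent in 6.5 means agreement and not mere notice.

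**What to change.** Amend section 6.5 and tie it to 9.1. State that, where there is immediate risk to the subject and knowledge of the arm affects care, that subject's envelope may be opened without waiting for the other party's consent. The reason is recorded, and the client is notified promptly without the arm being disclosed to staff who do not need it. Say that this is the written procedure, so that it does not count as a departure under 9.1.

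Keep the prior-consent step for any code break initiated by the client; this preserves the protection that the present rule gives against sponsor unblinding. Limiting prior consultation to non-emergency requests would not fit, because 6.5 considers unblinding only in severe emergencies and has no such category.

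The cost is a short protocol amendment and, at most, an occasional code break that proves unneeded, confined to one subject and documented. No sample size, analysis set or analysis method changes.
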